# Task-oriented training with computer gaming in people with rheumatoid arthritisor osteoarthritis of the hand: study protocol of a randomized controlled pilot trial

**DOI:** 10.1186/1745-6215-14-69

**Published:** 2013-03-09

**Keywords:** Arthritis, Hand function, Objects of daily life, Task-oriented training, Computer games

## Abstract

**Background:**

Significant restriction in the ability to participate in home, work and community life results from pain, fatigue, joint damage, stiffness and reduced joint range of motion and muscle strength in people with rheumatoid arthritis or osteoarthritis of the hand. With modest evidence on the therapeutic effectiveness of conventional hand exercises, a task-oriented training program via real life object manipulations has been developed for people with arthritis. An innovative, computer-based gaming platform that allows a broad range of common objects to be seamlessly transformed into therapeutic input devices through instrumentation with a motion-sense mouse has also been designed. Personalized objects are selected to target specific training goals such as graded finger mobility, strength, endurance or fine/gross dexterous functions. The movements and object manipulation tasks that replicate common situations in everyday living will then be used to control and play any computer game, making practice challenging and engaging.

**Methods/Design:**

The ongoing study is a 6-week, single-center, parallel-group, equally allocated and assessor-blinded pilot randomized controlled trial. Thirty people with rheumatoid arthritis or osteoarthritis affecting the hand will be randomized to receive either conventional hand exercises or the task-oriented training. The purpose is to determine a preliminary estimation of therapeutic effectiveness and feasibility of the task-oriented training program. Performance based and self-reported hand function, and exercise compliance are the study outcomes. Changes in outcomes (pre to post intervention) within each group will be assessed by paired Student *t* test or Wilcoxon signed-rank test and between groups (control versus experimental) post intervention using unpaired Student *t* test or Mann–Whitney *U* test.

**Discussion:**

The study findings will inform decisions on the feasibility, safety and completion rate and will also provide preliminary data on the treatment effects of the task-oriented training compared with conventional hand exercises in people with rheumatoid arthritis or osteoarthritis of the hand.

**Trial registration:**

ClinicalTrials.gov: NCT01635582

## Background

Rheumatoid arthritis (RA) is a chronic symmetric polyarthritis that can affect most synovial joints, but particularly the small joints of the hands, wrists and feet. In 80 to 90% of people affected with RA, the metacarpal phalangeal and proximal interphalangeal joints of the hand and wrist joints are involved [1,2]. Osteoarthritis (OA) affecting the hand is characterized by progressive cartilage loss and associated damage to joint margins and periarticular structures in the basal thumb, proximal interphalangeal and distal interphalangeal finger joints [3]. Pain, stiffness, fatigue, joint deformity, reduced joint range of motion and hand strength in RA and OA leads to limitations in common daily activities [1,4] and profoundly restricts the individual’s ability to participate in home, work, family and community life.

In spite of the advancements in pain or disease-modifying medications and joint surgeries, many people affected with RA do experience varying levels of difficulties in activities of daily living with reduced function and quality of life [5-7]. Nonpharmacological management is recommended in both RA and hand OA as an adjunct that often includes splinting, assistive devices, exercises, self-management techniques, joint protection and therapeutic modalities. The role and therapeutic effects of exercises in RA and OA populations have been discussed in many reviews [8-15]. A 2004 systematic review that included nine studies which evaluated any form of hand exercises on pain, stiffness, range of motion, grip and pinch strength, dexterity and function reported that there is no strong evidence for or against hand exercises in people with RA [16]. Another review concluded that an optimal hand exercise program in RA is yet to be established [17].

With respect to OA, the European League against Rheumatism added that recommendations for finger range of motion exercises, grip and pinch strength exercises or thumb muscle strengthening in hand OA was limited to level 4 expert opinion [13]. A 2010 review on randomized controlled trials and cohort studies from 1986 to 2009 reported moderate evidence for exercises in improving grip strength, range of motion, hand function and pain relief [14]. Another review with only three exercise treatment studies concluded that exercises do improve grip strength and hand function but have no effect on pain and stiffness [15]. Thus, with the limited number of studies with variability in the exercises prescribed, combination of additional therapeutic modalities, different outcome measures, exercise parameters (frequency, intensity, duration) and other methodological issues, it is difficult to arrive at definitive conclusions on the effects of range of motion or strength exercises on hand function in both populations. Although no strong evidence is available for the effectiveness of hand exercises, the theoretical basis and the purpose of prescribing exercises is to maximize function by preventing joint deformities, improving joint movement and strength of the grip muscles.

Most of the hand exercise programs prescribed for people with arthritis commonly include a variety of exercises aimed to improve the range of motion of the hand and wrist joints and/or to improve/maintain grip and hand intrinsic strength. However, other components of hand function such as dexterity are often not considered in hand rehabilitation programs [18]. In contrast, task-specific training with manipulation of common objects could also be incorporated for effective transfer into activities of daily living [18-20]. Low compliance and treatment adherence are the significant hurdles to be overcome in long-term exercise programs, especially in chronic illnesses such as arthritis. As a result, there has been an additional need for rehabilitation programs that provide motivation in order to continue and complete treatment regimes. Maximizing individual participation is seen as a main goal of any intervention that is central to functional success.

Since the 1980s, computer games have been used for therapeutic purposes in different patient populations [20-26]. Several recent studies have described the use and benefits of interactive computer games and it has been reported that they provide interesting and challenging activities [23], and are enjoyable, engaging and intrinsically motivating [20,23,25]. Utilizing biofeedback and motion-sensor technology advancements, an innovative, computer-based gaming platform interfaced by a commercial motion mouse that combines interactive computer games with handling and manipulation of day-to-day objects has been developed. A novel, task-oriented training program has also been designed that is aimed to extend the clinical rehabilitation experience to a home-based setting. The program utilizes an interface that allows use of many different common objects with diverse functional demands and physical properties to be incorporated into a personalized therapy program targeting dexterity, graded finger mobility, endurance and hand strength training. This opens up an exciting possibility for affordable and scientifically motivated improvements in arthritis rehabilitation.

Dexterity skills involving handling and manipulating objects with the fingers and hand are important for nearly all activities of daily life, such as dressing, grooming, eating, use of utensils and implements, and participation in play, hobbies and chores. These activities require manipulation of objects with a wide range of physical properties (size, shape, weight, inertia) and often require a high degree of precision, where small deviations in timing or endpoint accuracy and positioning/orientation of the object leads to complete disruption of performance. In a study by Guzelkucuk and colleagues on 36 young adults with hand injuries, a hand exercise program that included passive, active range of motion and strengthening exercises was compared with training of targeted functional activities such as using a spoon, rolling a cylinder, and locking and unlocking a door key [18]. Improved hand function was reported in the group that received these task-specific functional activities. The authors also concluded that activities aimed at dexterity should be incorporated into hand exercise rehabilitation, which would increase the transfer to life role participation. Building on a similar concept, the novel training program will adopt the following principles of task-oriented approach [19,27]: functional movements directed towards normal day-to-day activities, hobbies and work via manipulation of real-life objects; personalized treatment goals and training loads based on individual needs and abilities; rehabilitation focused on acquisition of skills and active patient participation for performance of meaningful and relevant tasks of daily life; and repetitive training to increase endurance and intensity of practice. In consensus with the general opinion and current practice of the use of mobility exercises in the management of RA/OA affecting the hip, shoulder and knee [28-30], we also expect that exercises involving graded mobility of the joints of the hand and wrist could improve hand function and reduce pain and stiffness in people with RA or OA of the hand. Exercise repetition as tolerated, endurance and strength are also other key components of the program.

Modern concepts of training using a task-specific approach are achieved by incorporating a wide range of common objects/tools/utensils used in daily life activities. Specifically, the therapy consists of manipulating common daily objects that have been instrumented with a motion sensor which seamlessly transforms each object, tool or utensil into a computer input device. A low-cost motion-sense mouse has been chosen for this purpose (Gyration air mouse Elite; SMK-Link Electronics, Camarillo, CA, USA). This mouse is small with gyroscopic and accelerometer sensors that are used to derive angular displacement signals. The motion signals are used in a manner identical to a computer mouse to control onscreen cursor motion. The motion mouse is secured by Velcro to many different objects, and this simple method allows object natural motions to be used as the computer input device. This allows manipulation of each object to play nearly any computer games. A wide range of common objects can be instrumented with the mouse. Most of the objects can be directly instrumented (Figure 1A) and a few small-sized objects require a slightly modified structural set up (Figure 1B).

**Figure 1 F1:**
[figure not shown]
**Instrumentation of objects.** (**A**) A coffee mug is instrumented with the motion sense mouse using Velcro strips. (**B**) A turning knob is instrumented with the mouse using a wooden block, dowel, rubber pad and Velcro strips.

Common objects of daily life have different physical, functional and ergonomic properties. Taking advantage of these properties, objects can be selected to train dexterity, graded mobility in metacarpal phalangeal, interphalangeal and wrist joints, or strengthen finger and wrist muscles. A framework (Figure 2) has been developed for selecting therapeutic objects for specific therapeutic values. The application allows manipulation of objects of any shape (cylindrical, spherical, conical and rectangular) or size (small, medium and large). A wide range of small to large objects can be used to train dexterous functions involving the use of two, three or four fingers or the whole hand, wrist and forearm in order to improve task accuracy, precision and movement quality/efficiency. Training of such skills are expected to emulate many daily functional activities such as holding/manipulating fine, medium and large objects, and cylindrical or spherical objects, turning a door key, doing up buttons, or pulling up/down zippers during dressing. A bottle cork, salad tongs, door knob, key, and fine beads are a few objects that can be selected to train fine manipulations. Large-sized balls, large–medium-sized scissors, a coffee mug, large–medium–small diameter paper rolls and sponge foam cylinders can be selected for gross manipulations. In addition to dexterity, strength training needs to be included because hand strength is also needed to perform many daily tasks requiring a strong grip, such as carrying heavy items, opening tight jars and turning large knobs.

**Figure 2 F2:**
[figure not shown]
**Framework for selecting personalized therapeutic objects for the task**-**oriented training program.**

Any commercially available computer game that requires mouse movements in the *x*, *y* or both axes can be used in the training program. Many commercial computer games are inexpensive, suitable for all ages and are easy to use. Computer games have tremendous potential as rehabilitation tools because they provide a wide range of challenges in precision level, movement speed, amplitude and direction while playing. Added features such as distracters, reaction time, strategies and difficulty levels, visual–spatial and cognitive challenges complement the basic game mode for more fun and motivation. However, it is important to identify games that suit the preferences and match the functional abilities of each individual. Games should also be simple, easily understandable and well balanced between skill, chance and strategy. Skill should be able to bring the best of the required rehabilitative movements, while chance and strategy keep the individual motivated. Also important is a large and ever-changing variety of games in order to maintain high levels of motivation and interest in participating individuals. Having easy access to a large number of inexpensive commercial games makes this possible. There are a number of online sites that have a large and diverse collection of games – for example, Big Fish Games, games2download. More than 100 computer games have thus far been tested and found suitable for this novel training program.

To date, no study has reported the use of task-oriented approach in people with arthritis affecting the hand. A pilot randomized controlled trial has therefore been planned to determine the preliminary estimation of the therapeutic effectiveness and to evaluate the feasibility of the task-oriented training in people with RA or OA of the hand.

### Hypotheses

The first hypothesis is that the experimental group receiving task-oriented training will show greater improvements in performance-based, self-reported hand function and reduction in pain and stiffness levels as compared with the control group receiving conventional hand exercises.

The second hypothesis is that the task-oriented training will be feasible in terms of compliance and treatment safety and will demonstrate better completion rate as compared with conventional hand exercises.

## Methods

### Study design

The study is designed as a single-center, parallel-group, assessor-blinded randomized controlled pilot trial.

### Inclusion criteria

Men and women aged between 30 and 60 years diagnosed with RA according to the American College of Rheumatology 1987 classification criteria or symptomatic OA of the hand according to American College of Rheumatology criteria will be recruited. They recruits should also be willing to give written informed consent, own a home computer and have a basic working knowledge of computers. A moderate level of difficulty perceived in performing certain activities of daily life, with a Disability of the Arm, Shoulder and Hand (DASH) score range of 25 to 50 out of the maximum score of 100, will be an added criterion.

### Exclusion criteria

People will be excluded if they present with any of the following features: recent surgeries (<6 months) in the dominant hand; problems with vision or hearing; recent changes in drug regimen <3 months; major diseases of the heart, lungs or liver; fixed finger joint deformities; and DASH scores <25 or >50.

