### Outcome measures

#### Primary outcome measure

The primary outcome measure will be the Arthritis Hand Function Test, an 11-item performance-based test that measures grip and pinch strength, dexterity, applied strength and dexterity in people with arthritis. Test–retest reliability of the Arthritis Hand Function Test measured by the intraclass correlation coefficient in 20 individuals with RA ranged from 0.53 to 0.96; inter-rater reliability ranged from 0.89 to 1.0. Test–retest reliability in 26 individuals with OA ranged from 0.7 to 0.96; inter-rater reliability ranged from 0.99 to 1.0 [38,39].

The peg-board dexterity test measures the time taken in seconds to place and remove nine pegs into the nine holes. Applied dexterity is the total time taken (seconds) to complete the following tasks: lacing a shoe, tying a bow, fastening/unfastening four buttons, fastening/unfastening two safety pins, cutting putty with a knife and fork, and manipulating coins into a slot.

Applied strength will be measured by the total number of soup cans lifted in a tray and the volume (ml) of water lifted in a pitcher.

Grip strength of the dominant hand will be clinically tested using a handheld dynamometer (Biometrics isometric hand dynamometer G100; Biometrics Ltd, Cwmfelingach, Gwent, UK). Grip strength will be recorded in kilograms and the best score out of the three consecutive trials will be used for analyses. Similarly, three-point pinch strength will be measured using a pinch meter (Biometrics precision pinch meter P200; Biometrics Ltd).

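### Eligibility does not require the dominant (measured) hand to be affected, and the surgical exclusion leaves out the other hand, on which several outcomes also depend

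*Protocol article*

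**What the plan says.** **Disease.** The Inclusion criteria admit people "diagnosed with RA according to the American College of Rheumatology 1987 classification criteria", with no hand or side stated, or with osteoarthritis: "symptomatic OA of the hand according to American College of Rheumatology criteria will be recruited". Again no side is given. The functional criterion is a DASH score of 25 to 50, which is not specific to one hand. The abstract adds hand involvement, but no side: "Thirty people with rheumatoid arthritis or osteoarthritis affecting the hand will be randomized".

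**Surgery.** The Exclusion criteria list "recent surgeries (<6 months) in the dominant hand". Surgery on the other hand is not mentioned.

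**Measurement.** Under Primary outcome measure: "Grip strength of the dominant hand will be clinically tested using a handheld dynamometer". Pinch follows: "Similarly, three-point pinch strength will be measured using a pinch meter". This implies the dominant hand but does not say so. Applied dexterity is a timed set of tasks that includes "lacing a shoe, tying a bow, fastening/unfastening four buttons, fastening/unfastening two safety pins, cutting putty with a knife and fork". Applied strength is a tray lift and a pitcher lift. No side is given for these.

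**Allocation and analysis.** Randomization is 1:1, computer-generated and concealed in sealed envelopes, and a blinded assessor evaluates the outcomes. Stratification, if used, is by RA or OA. The Statistical analysis plan section tests pre-to-post change within each arm with paired tests, and compares the arms after the intervention with unpaired tests. Thirty people are planned, without a formal sample size calculation.

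**The concern.** Two of the stated rules name a side and the disease criterion does not, so they fit together poorly.

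First, the hand that supplies strength data is chosen by dominance, not by disease. A right-handed person with symptomatic osteoarthritis in the left hand only, and a DASH score in range, meets every listed criterion. That person's grip is then recorded in an unaffected hand, which probably has less to gain from training. Grip is a component of the primary test and is named among the analysed outcomes.

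Second, the exclusion protects the hand used for grip but not the other hand. Tying a bow, using a knife and fork and lifting a tray normally take both hands, and DASH covers daily activities as a whole. Someone two months after surgery on the non-dominant hand can enter and may improve in these outcomes for reasons unrelated to either programme. The protocol otherwise aims for a stable and homogeneous baseline: it excludes recent drug changes and uses the DASH range to limit heterogeneity.

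At stake is the trial's preliminary estimate of effectiveness: attenuation in the strength items, and extra noise and inflated within-arm gains in the two-handed tasks and DASH.

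**Working it through.** The plan has no figure to reproduce: it states no power, effect size or SD. The check is a comparison of the rules, followed by a scale illustration on assumed inputs.

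**1. Which hand each rule names**

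| Rule | Hand |
|---|---|
| Inclusion, RA | none stated |
| Inclusion, OA | the hand, no side |
| Inclusion, DASH 25 to 50 | not tied to one hand |
| Exclusion, recent surgery | dominant only |
| Grip | dominant |
| Pinch | dominant by implication |
| Applied dexterity, tray lift | normally both |
| DASH | not tied to one hand |

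The surgical exclusion and grip name the same hand, so for grip (and by implication pinch) recent surgery on the measured hand is excluded. Two gaps remain: disease is not tied to the measured hand, and recent other-hand surgery is admitted.

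**2. Dilution of the strength effect**

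Let f be the share whose measured hand is unaffected, and r the response of an unaffected hand as a fraction of that of an affected hand. Neither is in the document. The expected effect is multiplied by 1 − f(1 − r).

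- r = 0: f = 10%, 20%, 30% gives 0.90, 0.80, 0.70.
- r = 0.5: f = 10%, 20%, 30% gives 0.95, 0.90, 0.85.
- r = 1: no dilution.

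For scale, with r = 0, 15 per arm, SD fixed at 1, two-sided 0.05 and the normal approximation, power is:

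| True effect d (assumed) | f = 0 | 10% | 20% | 30% |
|---|---|---|---|---|
| 0.5 | 27.7% | 23.3% | 19.4% | 15.8% |
| 0.8 | 59.1% | 50.5% | 41.8% | 33.5% |
| 1.0 | 78.2% | 69.3% | 59.1% | 48.3% |

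**3. Recovery after other-hand surgery, within one arm**

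Training sessions fall within 7 to 10 days after baseline and the home programme lasts 6 weeks, so the interval to the final visit is about 7 + 42 = 49 to 10 + 42 = 52 days. If m of 15 people each gain g SD from recovery (both assumed), the arm's mean change moves by m × g / 15.

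- m = 1: g = 0.5, 1, 2 gives 0.03, 0.07, 0.13 SD.
- m = 2: 0.07, 0.13, 0.27 SD.
- m = 3: 0.10, 0.20, 0.40 SD.

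These figures apply to within-arm change only. The between-arm test is stated on post-intervention values, where a person's final level counts, not the gain.

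**4. Recovery after other-hand surgery, between arms**

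If k such people are among the 30, the number in one arm of 15 is hypergeometric. The expected difference in counts between arms is 0 for every k, so there is no systematic bias. The chance that the arms differ by two or more is:

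- k = 1: 0.
- k = 2: both in the same arm, 14/29 = 48.3%.
- k = 3: all three in the same arm, (14/29) × (13/28) = 22.4%.
- k = 4: 59.8%.

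**The case against.** The main points on the other side, and what stands of each:

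- **The surgical rule does match the measured hand.** A reader might infer that surgical recovery is uncontrolled in the hand that is measured. For grip, and by implication pinch, the text says otherwise. This stands, and the surgical point is confined to the applied tasks and DASH.
- **Randomisation protects the comparison.** A reader might also infer that recovery can pass as a treatment effect. The hypothesis is comparative, and concealed 1:1 allocation spreads recovery equally in expectation. This stands. What remains is the uncontrolled within-arm tests and chance imbalance, and in a trial of 30 any prognostic factor can be unbalanced by chance.
- **One-sided disease may be uncommon.** The Background opens: "Rheumatoid arthritis (RA) is a chronic symmetric polyarthritis". It also gives 80 to 90% hand and wrist involvement in RA. This makes the gap mainly an OA matter. It does not close it, because OA is half of the eligibility definition and no share of OA participants is fixed.
- **An unaffected hand may still gain strength.** Both programmes include strengthening, and nothing in the document sets the response at zero. This stands: the 1 − f figure is the extreme case, and dilution works against finding an effect and does not create one.
- **A fixed dominant-hand rule is reproducible, and an article condenses screening detail.** Both are fair. The point does not depend on missing detail, though. The article states a side for surgery and for grip, and those stated rules admit the mismatched cases.

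**Conclusion.** The point holds in a limited form. The listed criteria admit people whose measured hand is unaffected, mainly people with one-sided hand OA. This would probably dilute the effect on grip and, if it is also taken on the dominant hand, pinch. They also admit people recovering from recent surgery on the non-dominant hand, whose recovery can inflate pre-to-post change in applied dexterity, the tray lift and DASH, and can add chance imbalance with about 15 per arm.

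The document does not support a claim of systematic between-arm bias, nor a claim that the surgical rule misses the hand used for grip.

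The size cannot be fixed, because the document gives neither the share with one-sided disease nor the number with recent other-hand surgery. The illustrations (a loss of up to 30% of the strength effect, and within-arm shifts of 0.03 to 0.40 SD) rest wholly on assumed inputs, and either problem could be nil if no such person enrols. For a feasibility pilot without formal sizing, this is a cheap improvement and not a threat to the trial.

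**What to change.** 1. In the Exclusion criteria, extend the surgical item to surgery within 6 months in either hand.
2. In the Inclusion criteria, add that the dominant hand, where strength is measured, is affected by RA or OA. Under Primary outcome measure, say explicitly that pinch is also taken on that hand.
3. The trial is ongoing, so for people already enrolled record the affected side and any hand surgery in the 6 months before baseline. Run a sensitivity analysis without the mismatched cases: those with an unaffected dominant hand for grip and pinch, and those with recent other-hand surgery for applied dexterity, applied strength and DASH. Both features are fixed before allocation, so dropping these people does not undo the randomised comparison, although it makes a small sample smaller.

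The alternative of measuring strength on an index hand, such as the more affected one, is a debatable trade. It would mix dominant and non-dominant values in an unpaired comparison of post-intervention levels and could add between-person variance.

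The cost is two lines of text, two baseline items and one extra analysis. The downside is a few more screening failures and a slightly narrower population.
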